### Qualitative interviews

After the end of the interventions, qualitative data will be collected from a subgroup (n=15–20) to evaluate the interventions from the participants‘ perspective. This will be done through semi-structured, guideline-based interviews (lasting approximately 20–30 min) with narrative components. The areas of interest include subjective experiences with the interventions, the perception of the illness and its impacts. Participants will be selected equally from both groups based on predefined criteria (eg, gender, adherence to the therapy programme). The interviews will be transcribed using software (noScribe) and analysed using qualitative content analysis according to Kuckartz in MaxQDA software.

### Data management

All data were collected and managed using the REDCap system. The REDCap database was programmed to ensure data quality through built-in validation rules and logic checks. Comprehensive strategies will be implemented to promote participant retention and ensure complete follow-up throughout the study. All reasonable efforts are made to maintain participant engagement, including regular communication, flexible scheduling and reminders. In cases where participants discontinue or deviate from the intervention protocol, relevant outcome data will continue to be collected as specified in the study protocol, whenever possible. These measures are intended to maximise data completeness and uphold the integrity of the study findings.

### Statistical analysis

All analyses are based on the intention-to-treat population, that is, all participants included in the study are analysed in the group to which they were originally assigned, regardless of the treatment they actually received. Missing values are handled using multiple imputation. The multiple imputation procedure will be conducted using R (V.4.3.1), employing the ‘missForest’ package for handling missing data.^91^ The multiple imputation procedure using the ‘missForest’ package involves handling missing values by employing a non-parametric approach. This package uses a Random Forest algorithm to predict missing values based on the observed data, accommodating both numerical and categorical variables. Through iterative variable iterations, missing values are imputed by leveraging predictions from the remaining variables within the dataset. In addition, a per-protocol analysis is conducted as a sensitivity analysis. The per-protocol population is defined as all participants who provide data at the respective time point and participate in at least 8 of the 12 intervention appointments.

The primary outcome measure is analysed confirmatory using a univariate analysis of covariance, in which the primary outcome measure is modelled as a function of group allocation (fixed factor), study centre (binary covariate), treatment credibility and expectation (linear covariates) and the respective baseline values (linear covariate). Within this model, the adjusted group difference and its 95% CI are estimated and tested for superiority of the intervention over the control group using a two-sided t-test at the α=0.05 level. The secondary end points are analysed exploratively (without correction for multiple testing) using the same models as the primary end point. To estimate the clinical significance of the results, change scores and effect sizes (Hedges’ g) are calculated for between-group comparisons.

HRV parameters within groups will be compared at two different time points using a Wilcoxon signed rank test. The results will be presented as medians and IQRs, Hodges-Lehmann estimator (HLE) of the differences, 95% CI and effect sizes r. A comparison between groups will be undertaken by examining the HLE, the 95% CI and the effect sizes r simultaneously.

All analyses will be conducted using R V.4.3.1, with the ‘psych’‘ package used for psychometric assessments.^92^

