### Sample size calculation

The study is powered to detect a minimal clinically relevant effect of 3.3 points on the CFQ.^61^ Based on an SD of 4.4 in a sample of patients with post-COVID-19 syndrome and fatigue diagnosed by CFQ,^62^ the estimated effect size is d=0.75. Assuming this effect, a two-tailed independent t-test with a significance level of α=0.05 requires a total of 78 participants to detect a group difference with a power of 90%. In order to avoid a possible loss of power due to a dropout rate of up to 20%,^63^ it is planned to include 100 participants in the study and assign them to the two study groups in a 1:1 ratio. Sample size calculation was performed using the ‘pwr’ package in R V.4.3.1.^64^

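### The procedure labelled multiple imputation is a missForest prediction fill with no random draw, so the confirmatory 95% CI is too narrow when week-12 fatigue scores are missing

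*Protocol article*

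**What the plan says.** Under Statistical analysis, the protocol article sets an intention-to-treat analysis ("All analyses are based on the intention-to-treat population, that is, all participants included in the study are analysed in the group" of original assignment) and states: "Missing values are handled using multiple imputation". It then names the tool, "employing the ‘missForest’ package for handling missing data", and describes how it works: "This package uses a Random Forest algorithm to predict missing values based on the observed data, accommodating both numerical and categorical variables". The method iterates over variables, and "missing values are imputed by leveraging predictions from the remaining variables within the dataset".

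The completed data feed the single confirmatory test. "The primary outcome measure is analysed confirmatory using a univariate analysis of covariance", adjusted for group, centre, credibility, expectation and baseline, and "the adjusted group difference and its 95% CI are estimated and tested for superiority of the intervention over the control group" at two-sided 0.05.

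The section's one stated sensitivity analysis is per-protocol. It is restricted to participants who have data at the time point and attended at least 8 of the 12 sessions. The Sample size calculation section allows for up to 20% dropout among 100 participants.

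**The concern.** Label and procedure do not match. Multiple imputation draws each missing value at random from a predictive distribution, several times over, so that the spread between completed data sets carries the uncertainty about the missing values into the standard error. The procedure described here inserts a prediction. A forest prediction is an average over trees and lacks the residual scatter of a real outcome. The ANCOVA cannot tell predictions from observations: it counts all 100 participants as informative and sees too little residual variance.

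At stake is the primary result. With 20% dropout, up to 20 of 100 week-12 scores would be predictions analysed as data. If group is just one of many candidate predictors in the forest, predictions for the two arms are also pulled towards each other, which shrinks the estimated difference. The result will be read against a minimal clinically relevant difference of 3.3 points, so both the interval and the estimate matter.

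**Working it through.** **1. The plan's own sample size.** From the Sample size calculation section: difference 3.3, SD 4.4, two-sided alpha 0.05, power 90%.

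- d = 3.3 / 4.4 = 0.75.
- Two-sample t-test (noncentral t): 38.35, so 39 per arm and 78 in total; power at 39 per arm is 90.5%.
- Dropout: 78 / (1 - 0.20) = 97.5, so 98, against 100 planned.

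The figures reproduce; sample size is not in dispute.

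**2. Simulation set-up.** 1,000 trials per scenario, 50 per arm, SD 4.4, the protocol's ANCOVA covariates, week-12 scores missing in equal shares per arm. The missForest-type fill used 100 regression trees, a square-root number of candidate variables per split and group among the predictors; the averaged prediction was inserted once. The comparator was normal-model multiple imputation with 20 data sets and Rubin's rules.

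Assumptions not in the documents: baseline to week-12 correlation 0.5 (0.3 and 0.7 showed the same pattern in a 40-trial pilot), missing completely at random, and 12 or 26 predictors in the forest.

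**3. Results, true difference 3.3** (size of the difference; sign dropped):

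| Method | Missing | Mean estimate | Model SE | Actual SD of estimate | 95% CI coverage |
|---|---|---|---|---|---|
| Full data, 12 predictors | 0% | 3.30 | 0.78 | 0.78 | 95.2% |
| missForest-type, 12 predictors | 20% | 2.87 | 0.71 | 0.83 | 85.8% |
| missForest-type, 26 predictors | 20% | 2.72 | 0.71 | 0.77 | 85.6% |
| missForest-type, 12 predictors | 10% | 3.10 | 0.75 | 0.80 | 92.7% |
| Forest run 5 times and pooled, 12 predictors | 20% | 2.86 | 0.71 | 0.82 | 85.6% |
| Proper multiple imputation, 12 predictors | 20% | 3.28 | 0.89 | 0.89 | 95.2% |

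The simulation error of a coverage near 86% is √(0.858 × 0.142 / 1000) = 1.1 percentage points.

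- Shrinkage at 20%: (3.3 - 2.865) / 3.3 = 13%. At 10%: (3.3 - 3.096) / 3.3 = 6%. With 26 predictors, against that scenario's full-data mean: (3.256 - 2.723) / 3.256 = 16%.
- Width: 0.710 / 0.828 = 0.86 of the true sampling SD, and 0.710 / 0.890 = 0.80 of the SE from proper imputation.
- The model SE with 20% missing (0.71) is below the SE with nobody missing (0.78). Losing data appears to add precision.

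**4. How much of the shortfall is width and how much is shrinkage.** Normal approximation for the 20%, 12-predictor case: the CI half-width is 1.99 × 0.710 = 1.41. With no bias, coverage would be P(|Z| < 1.41 / 0.828) = P(|Z| < 1.70) = 91%. With the bias of 0.435 it is Φ((1.41 + 0.435) / 0.828) - Φ(-(1.41 - 0.435) / 0.828) = Φ(2.23) - Φ(-1.18) = 87%, close to the simulated 85.8%. Narrow width alone breaks the nominal level; shrinkage adds the rest.

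**5. No true effect, 20% missing.** Model SE 0.705 against actual SD 0.739; rejection rate 6.1% (simulation error about 0.8 points); coverage 93.9%.

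**6. A second simulation,** in SD units (n = 100, three centres, four auxiliary baseline variables, correlation 0.5, 20% missing completely at random), gives the same picture: a true 0.75 estimated as 0.66 (12% too small), model SE 0.159 against 0.188, coverage 87%, type I error 7-8%.

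**The case against.** Several points count against a broader criticism.

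- **Left to the full plan.** An article need not state the number of data sets or the pooling rule. That is right, and their absence alone would not be a finding. But the text names the package and describes a prediction fill, and pooling five forest runs left coverage at 85.6%, because the runs differ only by forest noise. An analysis plan that follows this text inherits the fault.
- **False positives.** A reader might infer that the 0.05 level collapses. It does not: 6.1% in one simulation (not clearly different from 5%) and 7-8% in the other. Shrinkage partly offsets the narrow SE. Rates of 12.9% at 20% missing and 8.5% at 10% arise if a regression mean that keeps the arm effect is filled in, but the trial does not plan that method. Power at 3.3 points stayed near 96-97%.
- **Certain attenuation.** A reader might infer that the yoga effect is bound to be pulled towards zero. The article does not say how group enters the imputation, so the shrinkage is conditional on joint imputation with group as one of many predictors.
- **Amount missing.** 20% is the planning maximum. The Data management section commits to retention measures and to collecting outcomes after participants stop or deviate from the intervention. At 10% the harm is much smaller; with nothing missing it is nil.
- **Symptom-driven dropout.** The safety rules let the intervention be interrupted for exacerbation, and one might infer informative loss. Interrupting treatment is not losing the week-12 questionnaire, and no calculation here rests on it.
- **Not every analysis is touched.** The per-protocol set has no imputed outcomes at its time point. It cannot isolate the imputation, however, because the attendance rule changes the population too.
- **Randomness.** A forest has bootstrap noise, so calling the fill deterministic is loose. What it lacks is a residual or parameter draw.

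**Conclusion.** The concern holds in limited form. The protocol article mislabels a random-forest prediction fill as multiple imputation, and the confirmatory ANCOVA would treat those predictions as data. At a true difference of 3.3 points the nominal 95% CI covers about 86% at 20% missing and about 93% at 10%. The group difference is about 13% and 6% too small if the arms are imputed jointly with group as one of many predictors. The coverage figures come from that same joint set-up, so they contain the shrinkage as well as the narrow SE.

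They also rest on a baseline correlation of 0.5, missingness completely at random and assumed predictor sets. The direction of the SE error does not depend on those exact values; the size does. The damage is to the interval and the estimate. The documents and calculations do not support a claim of serious type I inflation, lost power or informative dropout.

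**What to change.** Before the data are analysed, replace missForest in the Statistical analysis section with one of the following:

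- Multiple imputation with random draws, for example chained equations. The imputation model should contain group, centre, gender, baseline CFQ, and week-12 and week-24 CFQ. State the number of data sets, run the primary ANCOVA in each, and pool estimates and variances by Rubin's rules.
- A likelihood-based mixed model for weeks 12 and 24, which needs no imputation of the outcome.

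If missForest is kept for any purpose, stop calling it multiple imputation and do not base the confirmatory interval on it.

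The cost is a text change and a few lines of R; no new data are needed. Intervals become wider: at 20% missing the SE rises from about 0.71 to 0.89, which is the honest figure. Simulated power at 3.3 points was still 95.4% under proper multiple imputation. A delta-adjusted sensitivity analysis would be a useful extra, but it is optional and is not part of correcting this error.

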**Methods and analysis:**

A randomised controlled trial with 100 patients with persistent fatigue due to post-COVID-19 syndrome is being conducted at three study centres. Patients are randomised to two interventions, yoga and health education. Both interventions include 12 weeks of 90 min supervised group sessions and 60 min of home practice per week. The primary outcome measure is fatigue on the Chalder Fatigue Scale 12 weeks after randomisation. Secondary outcome measures include postexertional malaise (DePaul Symptom Questionnaire), health-related quality of life (Short Form Health Survey-12 Item Version, EuroQol 5-Dimension 5-Level Questionnaire), anxiety, depression (Hospital Anxiety and Depression Scale), stress (Perceived Stress Scale), sleep quality (Pittsburgh Sleep Quality Index), hand grip strength, laboratory parameters and adverse events. Physical activity analysis over 7 days using a body-worn sensor and 24-hour heart rate variability using a 3-channel ECG recorder are assessed exploratively. All outcome measures will be assessed 12 and 24 weeks after randomisation. In addition, health economic analyses as well as mediator and moderator analyses including self-reported body awareness, self-efficacy, personality traits and treatment credibility/expectations will be conducted. Furthermore, qualitative interviews at week 12 will be carried out.

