## Methods

### Study design

The study is designed as a multicentre, single-blind randomised controlled trial with two study arms. The outcome assessor is blinded to group allocation. The study protocol is reported according to the Standard Protocol Items: Recommendations for Interventional Trials guideline.^60^

The study centres are the Institute of General Practice & Interprofessional Care at the University Hospital Tübingen, the Robert Bosch Center for Integrative Medicine and Health at Bosch Health Campus Stuttgart and the Charité Integrative Medicine Outpatient Department at Immanuel Hospital Berlin-Wannsee. A period of 12 weeks after randomisation is scheduled per participant until the primary outcome measure is collected (figure 1). Sustainability will be assessed as a follow-up after 6 months.

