### Randomisation 

After completion of the measurements at week 0, eligible participants will be assigned to one of two study arms, the yoga group or the health education group, via block randomisation (stratified by gender and study centre) with randomly varying block length. The randomisation sequence was created by an external scientist who has no participant contact during the entire study using R software (V.4.3.1). The randomisation list will be kept password-protected and only the scientist creating the list has access to it. Allocation concealment is ensured by central randomisation via Research Electronic Data Capture (REDCap) software. Once a participant has been randomised by the study physician, their data can no longer be changed in REDCap. Neither the participants nor the study physicians nor the study coordinators have insight into the randomisation sequence.

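### The confirmatory model codes study centre as a two-level term, although the trial has three centres and stratifies randomisation by centre

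*Protocol article*

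**What the plan says.** The abstract (Methods and analysis) says that the trial "is being conducted at three study centres". Study design names them: the general-practice institute at Tübingen, then "the Robert Bosch Center for Integrative Medicine and Health at Bosch Health Campus Stuttgart and the Charité Integrative Medicine Outpatient Department at Immanuel Hospital Berlin-Wannsee". Under Randomisation, participants are allocated "via block randomisation (stratified by gender and study centre) with randomly varying block length", so centre is a stratification factor with three levels.

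Under Statistical analysis, the primary outcome is modelled on group as a fixed factor, on "study centre (binary covariate", and on "treatment credibility and expectation (linear covariates) and the respective baseline values (linear covariate". The two-sided 5% test of the adjusted group difference from this model is the confirmatory test. Secondary end points are explored without multiplicity correction, "using the same models as the primary end point".

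The article nowhere says that two centres are combined, names a reference centre or defines a grouping of centres.

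**The concern.** The article does state a coding for centre, so this is not detail left to the analysis plan. The stated coding does not fit the design in the same article: a three-level factor cannot be carried by one two-level covariate.

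An analyst who follows the text literally has to merge two centres or leave one out. Leaving one out would go against the intention-to-treat statement in the same section, under which everyone included is analysed. That leaves merging, which can be done in three ways (Tübingen with Stuttgart, Tübingen with Berlin, Stuttgart with Berlin). Each would in general give a somewhat different adjusted difference, standard error and p-value.

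Two things are at stake:
- **An open choice.** If the coding is settled only once outcomes are known, it can look data-driven even when it is not.
- **Precision.** Randomisation balances the arms within each centre. If merged centres differ in mean fatigue, that variance stays in the residual although the design has balanced it out of the comparison. The standard error is then too large.

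**Working it through.** **1. The plan's own figure.** Sample size calculation uses a "minimal clinically relevant effect of 3.3 points on the CFQ" and is "Based on an SD of 4.4 in a sample of patients with post-COVID-19 syndrome and fatigue".
- d = 3.3/4.4 = 0.75.
- A two-sample t-test with two-sided α = 0.05 and 90% power needs 38.35 per arm, rounded up to 39, or 78 in total. This matches the article.
- With 20% dropout, 78/0.80 = 97.5, rounded up to 98; 100 are planned.

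The sample size reproduces, and centre coding plays no part in it.

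**2. Degrees of freedom.** A factor with k levels needs k − 1 indicators. Three centres need 2; one binary covariate supplies 1.

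**3. Loss from merging, by formula.** Let R² be the share of outcome variance carried by the lost centre contrast. The documents give no between-centre differences, so 2–10% is an assumption. With arms balanced within centre:
- SE inflation = 1/√(1 − R²)
- actual type I error = 2[1 − Φ(1.96/√(1 − R²))]

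To put R² on the CFQ scale, assume three equal centres, a within-centre SD of 4.4 and two merged centres that differ by D points. Two thirds of participants then lie D/2 from their merged mean. The lost variance is (2/3)(D²/4) = D²/6, so R² = (D²/6)/(D²/6 + 4.4²), where 4.4² = 19.36. Solving for D gives D = √[6 × 19.36 × R²/(1 − R²)].

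| R² | SE inflation | Actual type I error | D (CFQ points) |
|---|---|---|---|
| 0.02 | 1.01 | 4.8% | 1.5 |
| 0.05 | 1.03 | 4.4% | 2.5 |
| 0.10 | 1.05 | 3.9% | 3.6 |

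The last row needs merged centres that differ by more than the 3.3 points for which the trial is powered.

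**4. Loss from merging, by simulation.** Assumptions: 100 participants in centres of 34, 34 and 32, SD 4.4, 20% random dropout, a true difference of 3.3 for power, no other covariates, 4000 runs per scenario.

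| D | SE, merged vs three-level | Power, merged vs three-level |
|---|---|---|
| 2 | 1.00 vs 0.98 | 90.3% vs 91.0% |
| 3 | 1.02 vs 0.99 | 89.6% vs 90.7% |
| 4.4 | 1.07 vs 0.99 | 87.8% vs 90.9% |

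At D = 4.4, a full SD, type I error is 3.5% merged against 4.8% with three levels. At D = 2 and D = 3 it is 5.2% against 5.4% and 4.3% against 4.9%; the simulation error is about √(0.05 × 0.95/4000) = 0.3 percentage points. Across all scenarios the mean estimated difference lies between 3.27 and 3.32 in size under both codings, so there is no bias.

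**5. Cost of three levels.** The model has an intercept, group, centre, credibility, expectation and baseline.
- 80 completers: residual df goes from 80 − 6 = 74 to 80 − 7 = 73; power at d = 0.75 goes from 0.9115 to 0.9114.
- 100 participants: residual df goes from 94 to 93; power is 96.0% either way.

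**The case against.** The best defence is that *binary covariate* is loose wording for 0/1 indicators, two of them for three centres. The sentence labels each term by type, and nothing says that a centre is merged or dropped. This reading cannot be excluded, so it would be too strong to say that the model cannot be run. But the same sentence uses the plural for credibility and expectation and the singular for baseline, and centre is in the singular. Even if shorthand was meant, the text needs correcting.

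It is also fair to say that the consequence is small and in the safe direction. That stands. Several stronger inferences are tempting, and the documents do not support them:
- **Bias or excess false positives.** No fixed coding produces either. The one non-conservative risk is choosing the merger after seeing results, and its size is not estimated here.
- **A linear trend across codes 1, 2, 3.** The sentence reserves *linear* for credibility, expectation and baseline.
- **Capturing instructors and course groups.** Yoga groups hold at most 11, so about 50 in the yoga arm means at least five groups (50/11 = 4.5). Yoga teachers and health educators also differ by arm. A centre main effect does not represent groups or instructors nested within arm.
- **Restoring the full stratified design.** Gender is also a stratification factor and is not among the listed model terms, so correcting centre alone would not do this.
- **A substantial loss of precision.** The 2–10% range is assumed, and baseline CFQ may already absorb part of any centre difference.

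**Conclusion.** The concern holds in a limited form. The stated coding of centre is wrong or, at best, ambiguous for a three-centre trial, and it sits in the only confirmatory model. The contradiction is internal to the article and needs no outside source.

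The numerical effect is modest. For merged centres that differ by up to 3 CFQ points, the power loss is about one percentage point. The larger figures need differences at or beyond the trial's own minimal relevant effect. All of these sizes rest on assumed centre differences, near-equal centres and an SD of 4.4. The reason to act is the undefined choice in the primary test more than the lost precision. A reader might infer that the primary result would be invalid; neither the documents nor the calculations support that.

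**What to change.** Under Statistical analysis, replace the binary description with study centre as a categorical factor with three levels (two indicator variables). Make the same change for the secondary end points that reuse the primary model. Record it before analysis, so that the coding cannot appear to follow from the results; the article expects the study to be completed by March 2026.

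If the authors did intend to combine two centres, they should say which two and why, also before analysis.

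The cost is one phrase and one residual degree of freedom. The required 78, the planned 100 and the power do not change.

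### HRV, an exploratory outcome, is tested only within each arm; the arms are then compared by inspection, with no between-arm estimate, interval or error rate

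*Protocol article*

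**What the plan says.** The Statistical analysis section of the protocol article gives HRV a paragraph of its own. The test is within-arm: "HRV parameters within groups will be compared at two different time points using a Wilcoxon signed rank test". The reporting follows from that test: "The results will be presented as medians and IQRs, Hodges-Lehmann estimator (HLE) of the differences, 95% CI and effect sizes r". The only sentence on yoga versus health education is "A comparison between groups will be undertaken by examining the HLE, the 95% CI and the effect sizes r simultaneously".

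The same section treats the other outcomes differently. The primary outcome is analysed by ANCOVA: "Within this model, the adjusted group difference and its 95% CI are estimated and tested for superiority". That model is then extended: "The secondary end points are analysed exploratively (without correction for multiple testing) using the same models as the primary end point".

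On status, the abstract lists the secondary outcomes and then says separately that activity and "24-hour heart rate variability using a 3-channel ECG recorder are assessed exploratively". On timing, it says "All outcome measures will be assessed 12 and 24 weeks after randomisation".

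**The concern.** In a randomised trial, the evidence on treatment is the difference between the arms. A change within one arm mixes any treatment effect with natural recovery and regression to the mean, and a signed rank test cannot separate them. Setting two within-arm results side by side does not remove the shared part in a controlled way. The reader sees two estimates, two intervals and two effect sizes, and has no rule for deciding when they differ.

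Two errors become possible. A difference may be claimed because one arm shows a clear change and the other does not, although the true changes are equal. Or a real difference may be dismissed because the two intervals overlap. Table 1 lists 11 HRV measures, to be analysed over day and night periods and over 5 min intervals within them, so the opportunity recurs many times.

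HRV also has some weight in the argument. Participants are not blinded, and the Discussion lists HRV among the objective measures that partly offset the reporting bias of self-report. It can do that only through a contrast between the arms.

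**Working it through.** **1. The plan's own figure.** The documents give no number for the HRV analysis. The sample size rests on fatigue alone: "The study is powered to detect a minimal clinically relevant effect of 3.3 points on the CFQ". With SD 4.4, d = 3.3/4.4 = 0.75. A two-sided t-test at α = 0.05 with 90% power needs 38.35, so 39 per arm and 78 in total, as the protocol states. Allowing for 20% dropout, 78/0.8 = 97.5, so 98, against 100 planned. With 100 randomised 1:1 and 20% lost, 40 per arm remain; with none lost, 50.

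**2. What the text supplies.**

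| | Primary and secondary end points | HRV |
|---|---|---|
| Test | Between groups (ANCOVA) | Within each group (signed rank) |
| Estimate | Adjusted group difference | Hodges-Lehmann estimate of the paired differences |
| Interval | For the group difference | For the within-group change |
| Rule for comparing arms | Two-sided test at 0.05 | None stated |

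**3. First illustrative reading: one arm significant, the other not.** Let both arms have the same true change and let p be the power of the within-arm test. The chance that exactly one arm is significant at 0.05 is 2p(1−p). The shared change, in SD of change, is an assumption, because the documents give no HRV variance or expected change. Here p comes from the noncentral t for a paired test.

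| Shared change (SD) | p, 40 per arm | 2p(1−p) | p, 50 per arm | 2p(1−p) |
|---|---|---|---|---|
| 0 | 0.050 | 9.5% | 0.050 | 9.5% |
| 0.2 | 0.235 | 36% | 0.284 | 41% |
| 0.3 | 0.457 | 50% | 0.548 | 50% |
| 0.4 | 0.694 | 43% | 0.792 | 33% |
| 0.5 | 0.869 | 23% | 0.934 | 12% |

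The maximum is 50%, at p = 0.5. The chance falls again as the shared change grows and both arms become significant. Simulation with signed rank tests (4000 runs per setting, 40 per arm) gave 9.6%, 49% and 24% at 0, 0.3 and 0.5 SD.

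**4. Second illustrative reading: the two 95% CIs must not overlap.** With equal standard errors s, the intervals separate when the estimates differ by more than 2 × 1.96 × s. The standard error of the difference is √2 × s, so the critical value is 2 × 1.96/√2 = 2.772. The false-positive rate is 2(1 − Φ(2.772)) = 0.0056, about 0.6%.

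For power with 40 per arm and a between-arm difference of 0.75 SD of change (the planning value for fatigue, borrowed only as a scale), the standard error is √(2/40) = 0.2236 SD and 0.75/0.2236 = 3.354.

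- Direct test: Φ(3.354 − 1.960) = Φ(1.394) = 92%.
- Non-overlap: Φ(3.354 − 2.772) = Φ(0.582) = 72%.

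**5. A direct comparison.** In the same simulations, a Mann-Whitney test on change scores had a false-positive rate of 4.6% to 5.2% with 40 or 50 per arm, whatever change the arms shared.

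**The case against.** The strongest reply is that HRV is exploratory. The abstract says so, the Objectives section does not name HRV or autonomic function, and no confirmatory claim is planned on it. This stands, and it limits the weight of the point. It does not remove it: the secondary end points are also analysed exploratively and still receive a between-group model. Exploratory status relaxes control of multiplicity; it does not turn two within-arm results into a comparison.

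A second reply is that the HRV subsection comes after the heading for secondary outcomes, so the ANCOVA sentence might already cover it. A reader might equally infer that HRV is a secondary end point denied the model its peers receive. Neither reading is well supported. The abstract lists HRV apart from the secondary outcomes, and the specific HRV paragraph governs. If ANCOVA was intended, that paragraph needs correcting anyway.

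Third, the percentages depend on decision rules that the protocol does not state. The sentence on comparing groups mentions neither significance nor overlap of intervals. This also stands: the figures illustrate an undefined procedure and are not properties of a stated test.

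Fourth, the article is a condensed account, and its wording does not expressly exclude a between-arm Hodges-Lehmann shift. But the estimator is introduced in the sentence that follows the within-group test, so its natural meaning is within-arm. This is a stated method, not a detail left to another document.

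**Conclusion.** The point holds as a correction to an exploratory analysis. As written, the HRV plan yields no between-arm estimate or interval, and its error rate is undefined. Depending on how the results are read, the false-positive chance could be anywhere from about 0.6% (non-overlapping intervals) to 50% (the worst case of one arm significant and the other not). The latter reading gives about 9.5% when neither arm changes. These values assume equal true change in the two arms, approximate normality and 40 to 50 per arm; the within-arm changes of 0 to 0.5 SD are assumptions.

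A reader might infer more than this. The documents do not support saying that the trial has a 50% error rate for HRV, because no rule is stated. Nor do they support saying that randomisation is abandoned: participants are still compared as allocated, only informally. The Discussion's remark on yoga and the autonomic nervous system cites earlier literature as rationale and is not a planned claim from these HRV data. The primary result, the sample size and the listed secondary end points are unaffected.

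**What to change.** Replace the last sentence of the HRV paragraph with a direct between-arm contrast at week 12 and at week 24. Either of these would do:

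- the trial's existing ANCOVA with the baseline HRV value as covariate, on a suitable scale where a measure is skewed, reporting the adjusted group difference and its 95% CI; or
- the between-arm Hodges-Lehmann shift in change scores with its 95% CI and a Mann-Whitney test.

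Keep the within-arm medians, IQRs and changes as description only, without tests, and label all HRV results as exploratory. Naming each follow-up also settles which time points are compared.

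The cost is a change of analysis wording: same data, same sample size, no new measurements. It should be made before HRV is analysed by arm; the article expects the study to be completed by March 2026.
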